**Fig. 3 Fig3:**
[figure not shown]
Phases of the PLACES supported employment intervention

#### IPS coaches

Certified IPS coaches, with a background in higher vocational education (e.g., social work) and a completed training from the Dutch IPS knowledge center “Phrenos,” will deliver the intervention. Additionally, they will receive a PLACES-training and guidance from a commercial organization specialized in reintegration after cancer (i.e., Re-turn). The PLACES-training includes two videos with information on cancer survivors’ unique problems and needs, information on the organization of cancer care, and on study-specific information. After this training, all coaches have the opportunity to ask questions and discuss uncertainties regarding the intervention or the study with the executive researcher ([name]). Also, intervision meetings will be held twice a year with all coaches to collectively discuss cases and to learn from one another. We aim to recruit coaches from various Dutch regions to ensure national coverage. Each coach will operate within their own region and use their existing extensive network of employers to find suitable jobs for participants. All coaches will be supported and monitored by the reintegration organization.

#### Content of the intervention

Participants in the intervention group will be assigned to the reintegration organization that will conduct the PLACES intervention. The intervention comprises three consecutive phases with possible phase relapse (Fig. 3). The intervention will last a maximum of 12 months, starting after randomization, with each IPS coach having a maximum workload of 67 h per participant. This workload encompasses all tasks of the IPS coach, including administrative tasks, looking for a job and reporting to the SSA.

After a participant has been registered at the reintegration organization, an IPS coach will be assigned, and an initial meeting will be scheduled within three working days. In the “Intake and Assessment” phase (*phase 1*), the purpose is to become acquainted and discuss the participant’s work background and preferences. During this 60-min face-to-face meeting, the IPS coach and participant will also discuss their roles and responsibilities throughout the intervention. If necessary, additional meetings can be scheduled until the objectives of phase 1 are fulfilled.

In the “Acquisition and Application” phase (*phase 2*), the IPS coach guides the participant in finding a suitable job, including searching for vacancies, interacting with organizations, and coordinating the application process. The IPS coach may also assign tasks to the participant that can lead to finding a suitable job (e.g., writing application letters or creating or updating a LinkedIn profile). Meetings with the IPS coach will, on average, take place once a week via video calls to update each other on any progress and determine necessary actions. As a guideline, the IPS coach aims to contact a potential employer within 30 days of the initial meeting.

Once a suitable job has been found, the “Placement and Support at the Workplace” phase (*phase 3*) starts on the first day of work, during which the focus is on sustainable integration. The IPS coach will provide personalized support, adapted to the participant’s needs, which may include providing contractual advice and ergonomic support, and addressing work-related issues. The frequency of these meetings will depend on the participant’s needs. Optionally, if the participant prefers to do so, the employer or manager can join meetings and participate in the intervention.

### (Occupational) care as usual

Participants in the control group will receive CAU from the SSA, which may involve for example meetings with a reintegration expert or insurance physician. The aim of such meetings is usually to discuss or evaluate work ability and opportunities for RTW. The CAU from the SSA could also include the utilization of external reintegration services, such as job search assistance or vocational rehabilitation services. There are no restrictions for participants in the CAU control group to seek help from these or any other rehabilitation or medical services.

## Study measures

An overview of all the measures and potential confounders, with detailed descriptions of the operationalization and the validated questionnaires, are presented in Table 2.

**Table 2 Tab2:** Outcome measures and their assessment methods

Construct	# items	Description	Operationalization
**Participant characteristics**			
Age^a^	1	Participant’s age in years	Continuous
Gender^a,b^	1	Participant’s gender, with response options: male, female, or other	Categorical
Marital status	1	Marital status of participants categorized as: not married, married without children, married with children, living together with partner, living together with partner and children, living together with others, single with children, divorced, widow/widower, or other	Categorical
Children living at home	2	Living arrangement of participants (alone or together) and the number of children living at home	Continuous
Level of education^a^	1	The highest level of education completed by participants with eight answer options according to the Dutch education system, grouped into low, middle, and high, based on the International Standard Classification of Education (ISCED-97)	Categorical
Income^a^	1	Annual income of participants, with response options: < €30,000, €30,000–€60,000, €60,000–€100,000, and > €100,000	Categorical
Financial necessity to work	1	Whether it is a financial necessity for participants to work [yes/no]	Dichotomous
Time since diagnosis^a,b^	1	Time since cancer diagnosis at time of inclusion, calculated from the day (or month, if day is unknown) of diagnosis	Continuous
Type of cancer diagnosis^a,b^	1	The type of cancer diagnosed with answer options: breast cancer, skin cancer, colon cancer, lung cancer, prostate cancer, and other	Categorical
Type of cancer treatment^a,b^	5	Types of cancer treatment(s) received (e.g., surgery, radiation, chemotherapy, hormonal therapy, or a combination), duration of treatment, current treatment, and future treatment (e.g., hormone therapy)	Categorical
Importance of work^a^	1	Importance of work measured on a visual scale from 0 (not important at all) to 10 (very important)	Continuous
RTW expectation^a^	1	Participant’s estimation of the chances they will be at work in 6 months on a scale from 1 (no chance) to 10 (very high chance)	Continuous
**Primary outcome measure**			
Paid employment	1	Whether participant has engaged in paid employment since the last questionnaire [yes/no]	Dichotomous
**Secondary outcome measures**			
Time until paid employment^c^	1	Duration in calendar days between randomization and the first day of returning to paid employment	Continuous
Change in working hours^c^	1	Comparison between number of working hours at different time points (T1-T3)	Continuous
Health related quality of life	12	The Short Form Health survey (SF-12) is a widely used and validated measure of health-related quality of life (47)	The scale comprises 12 items covering physical health and mental health. Per dimension, the scores are added and transformed into a scale between – and 100. Higher scores indicate higher health related quality of life
Quality of working life	23	The Quality of Working Life Questionnaire for Cancer Survivors (QWLQ-CS) measures (1) meaning of work, (2) perception of the work situation, (3) atmosphere in the work environment, (4) understanding and recognition of the organization, and (5) problems due to the health situation [29]	The 23 items result in a standardized score of 0–100, with higher scores reflecting a better quality of working life
Work ability	1	The Work Ability Index (WAI) is a validated measure of work ability of which the first question will be used assessing participants’ estimation of their current work ability compared to their lifetime best on a scale from 0 to 10 (0 = cannot work at all and 10 = full work ability) [30]	Continuous
Self-efficacy regarding RTW	11	The self-efficacy regarding RTW scale assesses participants’ confidence in successfully RTW after health-related absence [31]. The scale is reliable with a Cronbach’s alpha between 0.90 and 0.96	11 items rated on a six-point scale from ‘totally disagree’ to ‘totally agree’. The RTW-SE score, with higher scores indicating more self-efficacy in RTW, is computed as the mean score of these items
Type of (paid) employment		Current work situation of participant (e.g., full time, part time, voluntarily unemployed, partly work-disabled)	Categorical
**Cost-effectiveness measures**			
Social benefits	1	Social benefit received by participant categorized as sickness benefit, partial or full work disability benefit	Categorical
Intervention costs		The costs of the reintegration trajectories at the SSA are equal to the sum of 67 h × hourly rate × number of participants. The cost of each individual trajectory is the same	Continuous
Productivity^c^	4	iMTA Productivity Costs Questionnaire (iPCQ) measures productivity costs related to health conditions, capturing absenteeism, presenteeism and performance at work (49)	Continuous
Occupational healthcare consumption	1	An Adapted iMTA Medical Costs Questionnaire (IMTQ) will assess self-reported occupational healthcare consumption categorized by different professionals (e.g., labor expert, reintegration services, physical therapist) and the number of appointment with each professional (50)	Continuous

^a^Used as potential confounder

^b^Used for subgroup analyses

^c^Only completed by participants with employment

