#### Costs

A cost-utility analysis (CUA) will be performed from an occupational healthcare perspective. The occupational healthcare perspective includes all costs associated with the formal Dutch occupational healthcare sector; i.e., intervention costs, occupational healthcare costs, absenteeism costs, and presenteeism costs. Intervention costs will be determined using a micro-costing approach. This means that detailed data will be collected about the number of resources used for developing, implementing, and delivering the intervention, which will in turn be valued using their respective unit prices. Occupational healthcare costs for all participants will be measured through self-reported questionnaires regarding the participant’s use of occupational healthcare services (e.g., insurance physician, labor expert), which will also be valued using prices of professional organizations. Absenteeism and presenteeism costs will be measured using the self-reported iMTA Productivity Costs Questionnaire (iPCQ) [36] and will be valued using gender-specific price weights [31]. The return on investment analysis (ROI) will be performed from the payer perspective. The costs for the payer perspective include the costs made by the SSA to provide the intervention, including the difference in costs for the intervention between the intervention and control group. Benefits will be defined as the mean difference in benefits costs. Information on the individuals’ benefits costs will be derived from the self-reported questionnaires and information about employment status.

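### Reintegration support is costed on two bases (PLACES at 67 all-task coach hours, other services by self-reported appointments), so the ICER cost difference is not like for like

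*Protocol article*

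**What the plan says.** **PLACES.** The intervention-cost row of Table 2 (Cost-effectiveness measures) reads "The costs of the reintegration trajectories at the SSA are equal to the sum of 67 h × hourly rate × number of participants", and adds "The cost of each individual trajectory is the same". Content of the intervention gives the 67 h as a ceiling, "each IPS coach having a maximum workload of 67 h per participant", and states its scope: "This workload encompasses all tasks of the IPS coach, including administrative tasks, looking for a job and reporting to the SSA". The Costs section gives a different rule, micro-costing of the resources actually used. Table 3 (Dose delivered) has coaches log the hours they spend.

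**Other reintegration support.** Participants and recruitment requires everyone, controls included, to be eligible for an SSA reintegration trajectory (criterion 6). Under (Occupational) care as usual, control care "could also include the utilization of external reintegration services, such as job search assistance or vocational rehabilitation services". The measure listed for such use is the adapted iMTA medical costs questionnaire in Table 2. It names reintegration services among its examples and records "the number of appointment with each professional". The Costs section applies this self-report to all participants and values it at prices from professional organizations, without giving their level or content.

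**Where the costs go.** Intervention and occupational healthcare costs both enter the cost difference of the ICER (Costs; Cost effectiveness evaluation). The ROI uses what the SSA spends, "including the difference in costs for the intervention between the intervention and control group". Strengths and limitations expects no cost beyond that of current SSA reintegration interventions.

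**The concern.** A PLACES trajectory is charged for administration, job search and reporting as well as meetings. A usual-care trajectory of similar content is seen only through the meetings that the participant remembers. If each meeting is priced as contact time alone, the provider's other work is charged in one arm and not in the other. The cost difference then grows with the share of controls who receive a trajectory, for reasons of measurement and not of resource use.

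Two related problems follow. PLACES participants fill in the same questionnaire and may enter their coach meetings as reintegration services, although those meetings are already inside the 67 h. The ROI also needs the SSA's trajectory spending in the control arm, and Table 2, presented as the overview of all measures, has no item for it.

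Cost-effectiveness is one of the trial's two stated aims. The effectiveness analysis is not affected. The weakness lies partly in data collection, so an analysis plan could not fully repair it afterwards.

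**Working it through.** The document gives no hourly rate, unit price, control uptake, ICER or ROI, so there is no figure of the plan's to reproduce. The check is an identity in hours per participant at a common hourly rate.

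**Inputs from the document**
- 67 h per PLACES participant (Table 2; Content of the intervention).
- 82 participants per arm (Abstract, Methods).

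**Assumptions, not in the document**
- u: share of controls who receive a trajectory.
- A control trajectory uses 67 h, as PLACES does.
- c: share of that trajectory's full cost recovered by appointments × price. It equals the contact share of the work times the price loading per contact hour.

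**Step 1, the flat charge.** 67 × 82 = 5,494 coach hours are charged to the PLACES arm, whatever is delivered.

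**Step 2, the effect of two bases.**
- Like-for-like difference: 67 − 67u.
- Measured difference: 67 − 67uc.
- Gap: 67u(1 − c).

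| u | Like for like (h) | Gap, c = 0.3 | Gap, c = 0.5 | Gap, c = 0.7 | Gap, c = 1 |
|---|---|---|---|---|---|
| 0.25 | 50.3 | 11.7 | 8.4 | 5.0 | 0 |
| 0.50 | 33.5 | 23.5 | 16.8 | 10.1 | 0 |
| 0.75 | 16.8 | 35.2 | 25.1 | 15.1 | 0 |

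At u = 0.5 and c = 0.5 the measured difference is 67 − 16.75 = 50.25 h against 33.5 h, a gap of 16.75 h (50%). With u = 0 there is no gap. If c exceeds 1 the sign reverses: u = 0.5 and c = 1.2 give 67 × 0.5 × (−0.2) = −6.7 h.

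**Step 3, the price that closes the gap.** c = 1 needs a loading of 1 / contact share: 3.33, 2.0 or 1.43 if contact is 30%, 50% or 70% of the work.

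**Step 4, double counting.** Let d be the share of PLACES participants who report their coach meetings as reintegration services, valued with the same c. This adds 67dc to the PLACES arm. At d = 0.5 and c = 0.5 it adds 67 × 0.25 = 16.75 h. The term rises with c, so a price high enough to close the gap in step 2 makes double counting worse: at c = 1 and d = 0.5 it is 33.5 h. No choice of price settles both problems; the coach contacts have to leave the count.

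**Step 5, the ROI.** The cost term needs the number of controls with an SSA-funded trajectory and its cost. A non-zero count for reintegration services hints at some service, but does not show who paid for it, its type or its cost. No other row of Table 2 or Table 3 supplies this.

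**Step 6, the two rules for PLACES.** A flat 67 h with one cost per trajectory cannot also be micro-costing of what was used. If coaches average fewer than 67 h, the flat rule charges PLACES for undelivered hours.

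**The case against.** The best reply is that cost is quantity times price. An appointment count is only a quantity, and a price that carries the provider's non-contact time would put both services on the same footing. The prices are not described, and recall error can go either way. This stands: the direction is likely, not proven.

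Second, the 67 h row is worded for SSA trajectories in general and gives each the same cost. With the expectation of no additional cost, it could be read as covering usual-care trajectories too. The reading is possible but does not cure the problem. One would still need to know which controls had a trajectory, and reintegration services would still be counted by appointment as well.

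Third, no source is named for the ROI's control-arm cost, and the SSA's own figures may be intended. This stands as far as it goes. A reader might infer that the ROI is biased through the questionnaire, but the document never makes that link. It supports only that no listed measure supplies the cost.

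Fourth, an article condenses: the adapted questionnaire's items and its prices may be set out elsewhere. That is fair for the details, and they are not counted here as missing. The two units, and the two rules for PLACES, are stated methods.

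**Conclusion.** The point holds as a mismatch of measurement. Reintegration support enters the ICER cost difference as all-task provider hours for PLACES and as priced appointments otherwise. An overstatement against PLACES is the likely direction if prices leave out non-contact time. Neither its sign nor its size can be fixed from the document, and every hour figure above other than 67 and 67 × 82 rests on assumed uptake, recovery and trajectory size.

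A reader might infer that the cost difference is certainly and grossly inflated. For example, 75% uptake and 15 one-hour appointments per trajectory give 67 − 0.75 × 15 = 55.75 h against 16.75 h, or +233%. The documents do not support that. They give no uptake, appointment number, appointment length or control trajectory of 67 h. Pricing an appointment at one contact hour assumes the conclusion, and the percentage is large mainly because its denominator is small. Nor is the questionnaire a control-arm instrument: both arms complete it, which is why double counting is also possible.

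The conflict between the flat 67 h and micro-costing is firmer and needs no assumption. The change is worth making because it is cheap and serves one of the two aims.

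**What to change.** 1. In both arms, record whether an SSA-funded reintegration trajectory was started, and its type, by one item at T1–T3 or from SSA records.
2. Value each such trajectory on the same basis as PLACES: all provider hours, or the price that the SSA pays. Use the same record for the control-arm cost in the ROI.
3. Exclude SSA-funded trajectories and PLACES coach contacts from the per-appointment count, and say so in the questionnaire. Keep the count for other professionals, such as the labor expert, insurance physician and physical therapist.
4. Reconcile the flat 67 h rule in Table 2 with the micro-costing in Costs, using the hours in the coach logbooks.

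**Cost.** One added item with a small response burden, asked retrospectively of participants already past a wave, and a unit price for each trajectory type. The logbook hours are already to be collected.

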### Participant characteristics

Sociodemographic and medical data, including age, gender, marital status, household and number of children, level of education, income, financial necessity to work, type of cancer, time since diagnosis, and cancer treatment, will be collected at T0. Some of these parameters will solely be used to describe the study sample, while others are used as potential confounder(s) or for subgroup analyses (see Table 2).

### Primary outcome measure

The primary outcome measure of this study is paid employment [yes/no] at any point during the 12-month follow-up. Participants will be asked at T1–T3 whether they have worked in paid employment since the previous questionnaire.

### Secondary outcome measures

Secondary outcome measures will include:Time until paid employment, defined as the number of days between randomization and starting paid employment. To calculate this, participants will be asked about the date they started their new jobChange in working hours (if employed), measured by comparing the average numbers of hours worked weekly at different times of follow-up. For each work situation (e.g., part-time, voluntary), participants will be asked about the number of hours per week they work. The hours worked in paid employment will be used for the analysesHealth-related quality of life, measured using the Short Form-12 (SF-12), which includes the subscales vitality, physical functioning, bodily pain, general health perceptions, and physical role functioning [32]. For the economic evaluation, the participants’ SF-12 health states will be converted to utility values, ranging from 0 (quality of life equal to death) to 1 (quality of life equal to optimal health), using the tariff of Brazier et al. [33]. Then, quality-adjusted life years (QALYs) will be estimated using the “area under the curve approach”Quality of working life, measured with the 23-item Cancer-specific Quality of Working Life Questionnaire (QWLQ-CS), which comprises five subscales: (1) meaning of work, (2) perception of the work situation, (3) atmosphere in the work environment, (4) understanding and recognition in the organization, and (5) problems due to the health situation [34]Work ability, assessed with a single question of the Work Ability Index (WAI), asking participants to estimate their current work ability compared with their lifetime best (0, cannot work at all; 10, work ability at its best) [35]Self-efficacy regarding RTW, measured using the 11-item self-efficacy scale [29]Type of paid employment, defined by the work situation. This will be reported with descriptive statistics. Answer options are as follows: fulltime, part-time, self-employed, studying, retired, involuntarily unemployed, voluntarily unemployed, partially or fully work-disabled, employed but on sick leave, unemployed and on sick leave, household/caring for others, and “other”

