### Sample size calculation

In a previous study of unemployed patients with spinal cord injury, participants who received IPS were significantly more likely to return to paid employment than those in the CAU group (30.8%; 95% CI 21.8–41.6 versus 10.5%; 95% CI 5.2–19.7, respectively) [25]. Based on these data, a power of 80% and an alpha of 0.05, a total of 148 cancer survivors are required to detect the same difference of 20% between the two groups (nQuery Advisor 7.0). Accounting for a 10% loss to follow-up, we aim to include 164 cancer survivors.

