Differences between the intervention and control group in secondary outcomes will be analyzed using linear or generalized linear regression analyses. Effect sizes and their 95% confidence intervals will be reported for all outcomes. To analyze the secondary outcome “time until paid employment,” a Kaplan–Meier survival analysis will be performed, and differences between intervention and control group will be tested with the log-rank test. In addition, the Cox proportional hazard model, or accelerated failure time analysis if applicable, will be applied to estimate hazard ratios and the corresponding 95% CIs, and the median time until paid employment for the intervention and control group will be determined if possible. All statistical analyses will be conducted using the IBM SPSS Statistics 28.0 [39] or R statistical software version 4.1.3 [40], and the statistical significance will be determined at a two-tailed significance level of 0.05.

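### Working hours are compared between arms only among the employed, so this secondary contrast conditions on the primary outcome and is not protected by randomisation

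*Protocol article*

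**What the plan says.** The Secondary outcome measures section defines the outcome as change "in working hours (if employed), measured by comparing the average numbers of hours worked weekly at different times of follow-up". It adds that hours are asked for each work situation and that only hours in paid work enter the analysis.

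Table 2 describes the same outcome as "Comparison between number of working hours at different time points (T1-T3") and marks it with footnote c: "Only completed by participants with employment". No rule gives 0 hours to participants without paid work.

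On analysis, the Effect evaluation section states: "Differences between the intervention and control group in secondary outcomes will be analyzed using linear or generalized linear regression analyses". It promises effect sizes with confidence intervals for all outcomes and commits all analyses to intention to treat. The Discussion lists working hours among the secondary outcomes on which PLACES is hypothesised to be effective. Type of paid employment, by contrast, is explicitly reserved for descriptive reporting; working hours are not.

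**The concern.** Employment during follow-up is the primary outcome and the thing PLACES is designed to change. Restricting the hours comparison to people with a job selects on that outcome after randomisation. The employed PLACES group would then contain people who would not have worked under usual care, and the employed control group has no counterpart to them. A difference in mean hours between these groups mixes any effect on hours with a difference in who is counted.

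The comparison therefore cannot be intention to treat as the protocol promises. An intervention that raises the total amount of paid work could show shorter average hours, and a reader could take that for a disadvantage. It would also rest on a small and unbalanced part of the sample.

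**Working it through.** **Planning rates.** The Sample size calculation section gives "30.8%; 95% CI 21.8–41.6 versus 10.5%; 95% CI 5.2–19.7, respectively" and states "a power of 80% and an alpha of 0.05, a total of 148 cancer survivors are required". The target is a 20-point difference, and the test is at a "two-tailed significance level of 0.05".

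The figure of 148 can be reproduced with rates rounded to 31% and 11%, using the pooled-variance formula:

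- n = [1.96 × √(2 × 0.21 × 0.79) + 0.842 × √(0.31 × 0.69 + 0.11 × 0.89)]² / 0.20² = 63.9 per arm.
- With continuity correction: (63.9/4) × [1 + √(1 + 4/(63.9 × 0.20))]² = 73.6, so 74 per arm and 148 in total.
- Loss to follow-up: 148/0.9 = 164.4, stated as 164, or 82 per arm.

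The unrounded rates give 142 with the correction and 124 without. The primary sample size is not at issue; the rates are used below only to count who would have hours.

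**Who contributes.**

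- PLACES: 82 × 0.308 = 25.3. Usual care: 82 × 0.105 = 8.6. Together 33.9 of 164, about 21%.
- With 74 per arm after loss to follow-up: 22.8 and 7.8.
- The primary outcome counts employment at any point in 12 months, so the number in work at a single wave could be smaller.

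**How different the groups are.** Assume that everyone who would work under usual care would also work under PLACES. Then (30.8 - 10.5)/30.8 = 66% of the employed PLACES participants are added workers with no counterpart among employed controls.

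**Precision.** The smallest difference detectable with 80% power is (1.96 + 0.84) × √(1/25.3 + 1/8.6) = 1.11 SD with 82 per arm, and 1.16 SD with 74. With an assumed SD of 8 h, 1.11 SD is about 9 h/week.

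**Direction.** The documents give no hours, so these are assumptions. Those who would work in either arm work 24 h/week and PLACES does not alter their hours; added workers work h hours.

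- Employed-only mean under PLACES = (0.105 × 24 + 0.203 × h)/0.308, against 24 under usual care. The difference is 0.659 × (h - 24).
- Mean over all randomised, with 0 h for those without paid work = 0.105 × 24 + 0.203 × h, against 0.105 × 24 = 2.52. The difference is 0.203 × h.

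| h (h/week) | Employed-only mean, PLACES v usual care | Difference | All-randomised mean, PLACES v usual care | Difference |
|---|---|---|---|---|
| 12 | 16.1 v 24 | -7.9 | 4.96 v 2.52 | +2.4 |
| 16 | 18.7 v 24 | -5.3 | 5.77 v 2.52 | +3.3 |
| 20 | 21.4 v 24 | -2.6 | 6.58 v 2.52 | +4.1 |
| 24 | 24.0 v 24 | 0.0 | 7.39 v 2.52 | +4.9 |
| 28 | 26.6 v 24 | +2.6 | 8.20 v 2.52 | +5.7 |

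A simulation of 20,000 trials (74 per arm, SD 8 h, t-tests) was run for h = 12, 16, 20 and 24. The employed-only comparison showed significantly shorter hours under PLACES in 49%, 28%, 11% and 2% of trials. The all-randomised comparison showed significantly more hours under PLACES in 44%, 61%, 74% and 84%.

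**The case against.** Four counter-arguments deserve an answer.

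- **Footnote c says who answers an item, not who is analysed.** It also marks time until paid employment, which is analysed by Kaplan-Meier and Cox methods that would ordinarily keep people without a job as censored. This is fair: the footnote alone does not fix an employed-only analysis set. The qualifier in the outcome definition does point that way, however, and nothing in the article assigns zeros.
- **The outcome is named as a change, whereas the table above compares levels.** This stands in part. If the analysis is of within-person change across T1 to T3, stable jobs of 16 h and 28 h both score zero, and the hour differences above do not apply. The selection remains, because only people in work would supply the values. The definition does not settle which is meant.
- **The negative sign comes from assumed hours.** Correct. If added workers work as long as the others, the employed-only difference is nil; if longer, it is positive. The loss of randomised comparability does not depend on that assumption.
- **The reach is limited.** Correct. The primary outcome and time until employment do not rest on this contrast, and health-related quality of life, work ability and self-efficacy carry no such restriction.

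A reader might also infer that quality of working life is compared among workers only. The document does not say so: footnote c is not attached to that row and the text adds no such condition. Its subscales presuppose a job, which makes the restriction plausible, but it remains an inference.

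**Conclusion.** The point holds for working hours. As defined, the between-arm comparison conditions on employment after randomisation, which the protocol's own rates put at about 25 v 9 people, and it conflicts with the blanket intention-to-treat commitment.

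Under the assumptions shown, and reading the outcome as weekly hours at a wave, the employed-only difference lies between -7.9 and 0.0 h/week when added workers work 12 to 24 h, while the all-randomised difference lies between +2.4 and +4.9 h/week. A reversal of sign is therefore possible, but it is not shown to be likely in this trial.

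Two stronger readings are not supported. The trial's randomisation is not undermined as a whole; one secondary contrast is affected. Nor does the document establish an employed-only analysis of quality of working life.

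**What to change.** Define the outcome as weekly hours in paid employment at T1, T2 and T3 in all randomised participants, with 0 h for anyone not in paid work at that wave. Report the arm difference in mean hours with robust or bootstrap standard errors. Show hours among the employed by arm as description only, without a between-arm effectiveness test. Likewise, label any quality-of-working-life result that is limited to workers as descriptive.

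The cost is analysis wording. Work situation and hours per situation are already asked, so a zero is an observed value for anyone who returns the questionnaire; people who do not return it remain missing and should not be set to zero. The drawbacks are a skewed outcome with many zeros, and a mean difference that combines the chance of working with the hours worked, so it overlaps with the primary outcome. The descriptive table of hours among the employed helps the reader separate the two.
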